#### 5.1.1. Randomization

Patients will be randomly allocated in a 1 : 1 ratio to two intervention groups to receive acupuncture in combination with anti-Parkinson drugs or anti-Parkinson drugs alone. A randomization sequence will be generated by a statistician not participating in this trial, using SPSS Statistics 26.0 (IBM SPSS Statistics Inc., Chicago, USA). The assignment sequences will be concealed in sequentially numbered, sealed, opaque envelopes to ensure sequence confidentiality.

#### 5.1.2. Blinding

A single-blind method will be applied during stage 1 experiment to determine whether acupuncture has a placebo effect. In stage 2, considering the particulars of the acupuncture operation and the difficulty of implementing a blind method, both the participant and the physician will unavoidably know the treatment items delivered during the study. However, the outcome evaluators and statisticians will be blinded and not participate in the participant treatment process. Thus, bias in the research results would be reduced considerably.

#### 5.1.3. Setting

In stage 2, participants will be recruited from patients admitted to the First Affiliated Hospital of Guangzhou University of Traditional Chinese Medicine.

### 5.2. Interventions

#### 5.2.1. Acupuncture Group

Interventions for the acupuncture group in stage 2 will be the same as those in stage 1.

#### 5.2.2. Control Group

Participants in the control group will be required to obtain CMO and maintain the original dosage of their anti-Parkinson drugs. If the dosages need to be increased or decreased during the trial to relieve symptoms, the change will be recorded in the case report form.

#### 5.2.3. Outcome Measurements

HAMA score will be the primary outcome. The primary outcomes will be measured at baseline and week 4. Moreover, universality, feasibility, cost effectiveness, Hoehn–Yahr Rating Scale score, UPDRS score, and serological indicators will be considered the secondary outcomes. Hoehn–Yahr Rating Scale score, UPDRS score, and serological indicators will be measured at baseline and week 4. Universality, feasibility, and cost effectiveness will be measured at week 4. In addition, the universality and feasibility study will employ questionnaires administered by the physicians, and cost effectiveness will be calculated as the ratio of HAMA score improvement to treatment cost. Furthermore, side effects will be assessed during the trial. The timeline of the outcome measurements is shown in Table 2.

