## 5. Statistical Analysis

To ensure the integrity and accuracy of data, two statisticians will independently perform statistical analyses using Statistics 26.0 (IBM SPSS Statistics Inc., Chicago, USA), establish the database, and provide proofreading for logic. Enumeration data will be expressed as percentages, whereas measurement data will be expressed as mean ± standard deviation. A normality test will be performed for the measurement data. For variables that are determined to be regularly distributed, a *t*-test will be employed, and for those that are not, a rank-sum test will be utilized. The rank-sum test and nonparametric test will be employed for graded data, and the chi-square test will be applied to counted data. Repeated-measures analysis of covariance (ANCOVA) will be used for the UPDRS, Hoehn–Yahr, HAMA, and SF-36 scales. The rank-sum test will be applied to compare efficacy. Serological index values will be analyzed using covariance. Two-sided tests will be used for all hypothesis testing, with *P* < 0.05 as the standard of statistical significance.

Stage Two: if the efficacy of acupuncture with anti-Parkinson drugs for PDA is found to be better than that of the sham acupuncture, excluding the possible placebo effect of acupuncture, stage 2 will be conducted to assess the compliance, viability, universality, and cost effectiveness of acupuncture for PDA.  Figure 6 depicts a flowchart of the second step.Diagnostic criteria:  The diagnostic criteria for stage 2 are the same as those for stage 1Participant inclusion criteria:  The inclusion criteria for stage 2 are the same as those for stage 1Participant exclusion criteria:  The exclusion criteria for stage 2 are the same as those for stage 1

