## 6. Parkinson's Disease Rating Scale

### 6.1. Statistical Analysis

All data will be analyzed using intention-to-treat (ITT) analysis and the per-protocol set (PPS) for coherence. As in stage one, normality tests will be performed on the measurement data. A *t*-test will be performed for variables found to be normally distributed, and the rank-sum test will be used for those not normally distributed. The rank-sum test and nonparametric test will be used for the graded data, and the chi-square test will be applied to counted data. Repeated-measurements ANOVA will be used for the UPDRS, Hoehn–Yahr, HAMA, and SF-36 scales. The rank-sum test will be used to compare efficacy.

### 6.2. Ethical Issues in Stages 1 and 2

The trial will be conducted according to the guidelines of the Declaration of Helsinki.

The study was approved by the Ethics Committee of the First Affiliated Hospital of Guangzhou University of Traditional Chinese Medicine (No. K [2021] 021). All the participants will be asked to provide informed consent before participating in the trial.

### 6.3. Quality Control in Stages 1 and 2

A research workbook will be established. All the investigators will be trained and tested for conformance with preset standards before the beginning of each stage. Each participant will have a fixed physician and time points for treatment to ensure consistency in the intervention effect. Since the use of anti-Parkinson drugs will affect the physician's evaluation of patient symptoms, the participants will be evaluated for PD symptoms 4 hours after taking their medication.

All acupuncturists participating in this project have received formal education at Traditional Chinese Medicine universities, obtained physician qualification certificates, and possess more than 3 years of clinical experience in acupuncture.

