To reduce bias, we will use a rigorous allocation method with blinded patients, evaluators, and statistical analysts. We will also use a new type of sham acupuncture tool to avoid the placebo effect. Therefore, this trial will potentially provide valid clinical evidence. However, this study has certain limitations. First, owing to the nature of acupuncture, the operator cannot be blinded in this study. However, we will ensure the blinding of the participants, evaluators, and statistical analysts. Second, although we strictly require no increase or decrease of the medication dosage of the participants during treatment, it is difficult to monitor the self-medication of patients. Third, although a strict sample size calculation was carried out for this study, the participants will be recruited from only one hospital, which may lead to a lack of representativeness of the data.

Whether a treatment measure is suitable for clinical application and promotion needs to be comprehensively considered from the aspects of clinical efficacy, cost and economic benefits, patient acceptance, and feasibility. Therefore, this study has two stages. Stage 1 of this study hypothesizes that patients with PDA receiving acupuncture will have a reduction in anxiety as a result of adjustments to the HPA on the basis of excluding the placebo effect. Stage 2 of this study hypothesizes that acupuncture to relieve PDA has the characteristics of high feasibility, fewer side effects, high patient compliance, and reasonable cost effectiveness. It will not add additional economic burden to patients and their families while providing a curative effect and improving the quality of life of patients. It is a treatment method with clinical promotion and application value. The second stage is a supplement to the first stage. We designed this two-stage trial to observe whether acupuncture has clinical application value in the treatment of PDA.

The findings of this study will help to validate the effects and mechanism of acupuncture as a complementary treatment method for PDA. The study has the potential to provide strong clinical evidence as well as new guidelines for the treatment of PDA.

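### Stage 2 universality and feasibility questionnaires are assigned to physicians who, on the natural reading, are unblinded and involved in treatment, leaving two secondary outcomes open to avoidable interviewer bias

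*Protocol article*

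**What the plan says.** Section 5.2.3 makes HAMA the primary outcome of stage 2. It then ranks the others: "universality, feasibility, cost effectiveness, Hoehn–Yahr Rating Scale score, UPDRS score, and serological indicators will be considered the secondary outcomes". On timing, "Universality, feasibility, and cost effectiveness will be measured at week 4", and Table 2 likewise shows no baseline assessment for these three. On collection, "the universality and feasibility study will employ questionnaires administered by the physicians".

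Section 5.1.2 (Blinding) concedes that in stage 2 "both the participant and the physician will unavoidably know the treatment items delivered during the study". It then names the protection against bias: "the outcome evaluators and statisticians will be blinded and not participate in the participant treatment process". Section 6.3 (Quality Control in Stages 1 and 2) adds: "Each participant will have a fixed physician and time points for treatment".

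The role of these outcomes appears in two places. Section 5 says that, if stage 1 succeeds, "stage 2 will be conducted to assess the compliance, viability, universality, and cost effectiveness of acupuncture for PDA". Section 7 states the stage 2 hypothesis that "acupuncture to relieve PDA has the characteristics of high feasibility, fewer side effects, high patient compliance, and reasonable cost effectiveness".

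**The concern.** The plan does not leave open who collects universality and feasibility; it names the physicians. When someone involved in a patient's care asks whether that care was acceptable or practical, the patient may answer more favourably than on a private form. The person asking may also phrase or record answers in the hoped-for direction. Where that person delivered four weeks of needling, the pull is plausibly stronger than in a control arm that receives leaflets and continued medication.

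At stake is the part of stage 2 that goes beyond efficacy. These outcomes are formally secondary, but they belong to the stated reasons for running the stage and to the argument in section 7 that acupuncture is fit for wider clinical use. If the method of collection favours positive answers, that argument loses support in a way that no later analysis can repair.

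**Working it through.** No figure in the plan bears on this point, so the check sets the passages side by side.

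1. **Who collects.** Section 5.2.3 names the physicians, without saying whether they treat the participant.
2. **What the physician knows.** Section 5.1.2 puts the stage 2 physician, with the participant, on the unblinded side.
3. **What the safeguard is.** The same section contrasts that physician with evaluators who are blinded and stay out of treatment. Its claim that bias is considerably reduced rests on this separation.
4. **How physician and participant are linked.** Section 6.3 ties each participant to one physician for treatment, and says that the acupuncturists hold physician qualifications. In this protocol the person who needles is therefore a physician.

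Steps 1 to 4 make an unblinded physician involved in treatment the natural reading. On that reading, section 5.2.3 gives two outcomes to the role that section 5.1.2 keeps apart from outcome evaluation, and states no exception or safeguard.

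5. **Other readings.** If the physicians are instead the blinded evaluators, a questionnaire about the feasibility of acupuncture could reveal the arm to people meant to be unaware of it. These may include whoever rates HAMA, which is also due at week 4. If they are physicians who neither treat nor rate, neither problem arises, but the text does not say so.
6. **Can later data offset the bias?** No. The two outcomes are measured only at week 4, so there is no baseline value to adjust for.
7. **How far does it reach?** HAMA is protected by the evaluators of section 5.1.2. Cost effectiveness is calculated from HAMA improvement and treatment cost, not from these questionnaires. On the natural reading, then, the problem is confined to universality and feasibility.
8. **Size.** The document gives no questionnaire score, response proportion or success threshold for either outcome, so there is nothing from which to compute a bias.

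**The case against.** The strongest reply is that the identity of the physicians is inferred. The article's terms are loose: those who needle are called operating doctors, acupuncturists and acupuncture operators, and section 6.3 also speaks of a physician evaluating symptoms. Read with section 5.1.2, the questionnaire physicians could be staff outside treatment. This stands as a limit on the finding: the text supports a natural reading, not a certainty.

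A second reply is that the article does not say who answers, what is asked, or whether administering means interviewing or handing out a form, and that such detail belongs in the full protocol. This is fair, and its absence is not criticised here. What remains is the one thing the article does fix, namely who administers the questionnaires.

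Third, someone asking about the feasibility of acupuncture can hardly be kept unaware of who received it. This also stands. The part of section 5.1.2 that can sensibly be held to is that the evaluator takes no part in treatment.

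A reader might also infer that courtesy bias acts in the acupuncture arm alone. The documents do not support that: section 6.3 gives every participant a fixed physician, so controls may also answer to please theirs. Nor does the article say whether controls receive the questionnaires. A reader might further infer that the primary result is compromised; on the natural reading it is not.

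**Conclusion.** The concern holds in limited form. On the natural reading of sections 5.1.2, 5.2.3 and 6.3, universality and feasibility are collected by unblinded physicians involved in treatment. That does not fit the plan's own reliance on evaluators who stay out of treatment. The consequence is avoidable exposure of two secondary outcomes to interviewer or courtesy bias, plausibly larger in the acupuncture arm. Its size is unknown.

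Two assumptions carry this: that the physicians of section 5.2.3 are those of sections 5.1.2 and 6.3, and that patients answer more favourably to someone involved in their care. The second is general methodological reasoning, not something the document states. The point deserves correction because these outcomes are among the reasons given for stage 2 and the remedy is cheap.

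**What to change.** Amend section 5.2.3 to say that participants complete the universality and feasibility questionnaires themselves at week 4, after the HAMA rating. They return them in a sealed envelope that neither the treating physician nor the blinded HAMA evaluator opens. A participant who needs help with writing gets it from existing study staff who did not treat that participant.

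This works whoever the physicians were meant to be: it takes the treating physician out of the interview and keeps answers that reveal the arm away from the HAMA evaluator.

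The cost is a change of wording, a supply of envelopes and slightly more missing items than with interviews; no extra staff are needed. It does not remove expectation bias, because stage 2 participants know their treatment, and the report should say so when it interprets these outcomes.

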## 2. Materials and Methods

### 2.1. Trial Design

This study will be a two-stage clinical trial for Chinese patients with PDA. The first stage will be a randomized single-blinded controlled clinical trial with a sham acupuncture control, which aims to evaluate the efficacy of acupuncture. The second stage will be a randomized controlled clinical trial with blank control, which aims to analyze the efficacy, cost effectiveness, and compliance feasibility of acupuncture for PDA. The trial will be conducted at Guangzhou University of Chinese Medicine's First Affiliated Hospital in China.

Ethics committees at the First Affiliated Hospital of Guangzhou University of Chinese Medicine have accepted the study protocol, which will follow the Declaration of Helsinki. It has been registered with Current Controlled Trials (ChiCTR2100047253).

Stage 1 will be a randomized clinical trial using a sham acupuncture control.  Figure 1 depicts the flowchart for the first step.

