## 3. Interventions

### 3.1. Acupuncture Group

Participants assigned to the acupuncture group will receive twelve 30 min sessions of acupuncture (once every other day, four times a week for four weeks) with clinical monitoring only (CMO) and maintain their original dosage of anti-Parkinson drugs. If the dosages need to be increased or decreased during the trial to relieve symptoms, the change will be recorded on the case report form. Patients in the intervention group will receive needling at traditional acupuncture points, including GV 24 (*shen ting*), GV 29 (*yin tang*), bilateral HT7 (*shen men*), bilateral SP 6 (*san yin jiao*), and *Si Shen Zhen* (four acupoints, consisting of GV 21, GV 19, and 1.5 cun next to GV 20 bilaterally, with the width of the patient's thumb joint being taken as one cun). The acupoints' positions are described by the National Standard of the People's Republic of China's (GB/T 12346–2006) standard for the name and location of the acupoints, which was established in 2006. Acupuncture will be performed with disposable, sanitized stainless steel needles (Tianxie, Suzhou Medical Appliance Factory, Suzhou, China; 0.25 × 25 mm, 0.25 × 40 mm). GV 24 (*shen ting*), GV 29 (*yin tang*), and *Si Shen Zhen* adopt 0.25 × 25 mm acupuncture needles with a 45-degree angle. Bilateral HT7 (*shen men*) and bilateral SP 6 (*san yin jiao*) will use 0.25 × 40 mm acupuncture needles with a 90-degree angle. The selection and location of the acupoints are shown in Figure 2. After routine disinfection, the acupuncturist inserts the needles into the corresponding acupoints and stimulates all the needles by lifting, twirling, and thrusting to obtain the *de qi* sensation (a combination of feelings, such as numbness, soreness, and heaviness).

CMO will involve providing patients with general educational leaflets on dealing with anxiety that were retrieved from web portals of the French and Netherlands psychiatric associations.

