### 5.1. Sample Size

The sample size was calculated using the primary outcome, which is the shift in HAMA score from baseline. According to preliminary results, the mean HAMA score in patients who received acupuncture combined with anti-Parkinson drugs was 15.8, while it was 13.9 in patients who received anti-Parkinson drugs alone. According to PASS 15.0, a sample size comprising 74 patients (37 in each group) would have a power of 80% or more to identify a two-sided significance level of 5%. The overall sample size needed for the study is 82 (41 in each group), anticipating a 10% dropout rate. If a patient cannot adhere to a course of acupuncture, patient's condition suddenly worsens during the treatment process, and the treatment plan of anti-Parkinson drugs needs to be changed, the treatment will be stopped.

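### Stage 2 cost effectiveness is defined as improvement divided by cost with no between-arm difference, so the ranking of the arms also depends on background cost and background improvement

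*Protocol article*

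**What the plan says.** Section 2.1 of the protocol article describes stage 2 as a randomised comparison "which aims to analyze the efficacy, cost effectiveness, and compliance feasibility of acupuncture for PDA". Section 5.2.3 makes cost effectiveness a secondary outcome, timed by the sentence "Universality, feasibility, and cost effectiveness will be measured at week 4", and gives its formula: "cost effectiveness will be calculated as the ratio of HAMA score improvement to treatment cost". It does not say whether improvement and cost are taken per arm or as differences between arms, and it does not list the cost items. The stage 2 analysis methods in section 6.1 have nothing specific to cost.

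The arms share their background treatment. In section 3.1, which also governs stage 2, the acupuncture group is treated "with clinical monitoring only (CMO) and maintain their original dosage of anti-Parkinson drugs" in addition to the twelve sessions. For controls, section 5.2.2 says: "Participants in the control group will be required to obtain CMO and maintain the original dosage of their anti-Parkinson drugs". Section 3.1 describes the monitoring component as leaflets: "CMO will involve providing patients with general educational leaflets on dealing with anxiety". Table 2 labels the two regimens accordingly, with acupuncture as the only difference.

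The Discussion adds an economic expectation about acupuncture: "It will not add additional economic burden to patients and their families while providing a curative effect". That sentence does not bear on how the ratio is calculated, but it is a statement about added cost.

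**The concern.** The arms differ only by acupuncture, so the economic question is what the extra HAMA improvement costs. An average ratio answers a different question. It credits each arm with improvement that would have occurred without acupuncture and divides it by a cost that includes treatment common to both arms. Two settings with the same added cost and the same added benefit can then be ranked in opposite order because background drugs are dearer in one, or because controls improve more in one.

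Cost effectiveness is a named aim of stage 2 and part of the case the authors intend to make for wider use of acupuncture. As written, the measure could make acupuncture look better or worse than its added cost and benefit justify. It would also not show whether acupuncture adds to the economic burden, which needs the cost difference itself.

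**Working it through.** The documents report no cost and no cost-effectiveness result, so there is no figure to reproduce. The check is algebra on the stated formula, with assumed numbers for illustration.

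**Inputs**
- C: mean background cost per patient, common to both arms (assumed).
- A: mean added cost of acupuncture per patient (assumed).
- E1, E0: mean HAMA improvement with acupuncture and in controls, with E1 > E0 > 0.
- Gain E1 - E0 = 1.9 points: an assumed value, equal in size to the gap between the two stage 2 planning means in section 5.1 (15.8 - 13.9).

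**Average ratios, as the formula reads**
- Acupuncture: E1/(C + A). Control: E0/C.
- Acupuncture has the higher ratio if and only if E1/(C + A) > E0/C, that is E1·C > E0·C + E0·A, that is A/C < (E1 - E0)/E0.

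**Incremental form**
- Cost per extra HAMA point: (C + A - C)/(E1 - E0) = A/(E1 - E0). Neither C nor the level of E0 enters once the gain is fixed.

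**Break-even A/C for the same 1.9-point gain**

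| Control improvement E0 (assumed) | E1 | Break-even A/C | Incremental cost per point |
|---|---|---|---|
| 2 | 3.9 | 1.9/2 = 95% | A/1.9 |
| 4 | 5.9 | 1.9/4 = 47.5%, about 48% | A/1.9 |
| 10 | 11.9 | 1.9/10 = 19% | A/1.9 |

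**Effect of shared background cost alone** (assumed E0 = 4, E1 = 5.9, A = 300 units)
- C = 500: acupuncture 5.9/800 = 0.738 points per 100 units, control 4/500 = 0.800. Control ranks higher.
- C = 1000: acupuncture 5.9/1300 = 0.454, control 4/1000 = 0.400. Acupuncture ranks higher.
- Incremental cost in both cases: 300/1.9 = 157.9 units per extra point.

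**If drug cost were left out**
- The control denominator would be the cost of the leaflets. With an assumed 1 unit for leaflets, A = 1000 and E0 = 4, control would show 4/1 = 4 points per unit and acupuncture 5.9/1001 = 0.006. The contrast comes almost entirely from the tiny denominator.

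**The case against.** The strongest reply is that the formula is one clause in a condensed article. It does not say that the ratio is taken within an arm, and the authors may have meant the difference in improvement over the difference in cost. That is fair: the per-arm reading is inferred from the absence of any comparator. If the incremental meaning was intended, the method is sound and only the wording needs correcting. Cost items, perspective and interval methods could also sit in a fuller document. The formula itself, however, is fixed here, and it names no difference.

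Some stronger readings are tempting but not supported:
- A reader might infer that the control ratio is undefined. That requires drug cost to be excluded, and Table 2 describes control treatment as anti-Parkinson drugs plus CMO. On that description the denominator is not zero.
- A reader might infer that the ratio ignores what acupuncture adds. The break-even condition contains both A and E1 - E0, so the ranking depends on these and on background values as well.
- A reader might infer that a trial verdict could be reversed. No threshold, test or adoption rule is attached to this outcome.
- A reader might infer unstable or negative ratios for individual patients. The plan does not state patient-level ratios.
- A reader might put the section 5.1 means into the condition and obtain 15.8/13.9 - 1 = 13.7%. The text presents these as scores: "the mean HAMA score in patients who received acupuncture combined with anti-Parkinson drugs was 15.8". Entry scores are 14 to 29, so a mean fall of 13.9 in controls would take a patient from 14 to 0.1, or from 29 to 15.1. The 13.7% therefore rests on a doubtful reading, and the point does not need it.

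**Conclusion.** The concern holds in a limited form. Section 5.2.3 gives a formula that, read directly, is an average ratio for each arm, and this does not answer the incremental question that stage 2 poses. The ranking can change with background drug cost or background improvement while the added cost and added benefit stay the same: the break-even A/C runs from 95% to 19% as control improvement goes from 2 to 10 points at a fixed 1.9-point gain.

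The conclusion rests on three things: the per-arm reading, drug cost being counted in both arms, and acupuncture being both more effective and more costly. The algebra is exact under those conditions. The numbers illustrate it and are not estimates for this trial, since no costs are given. Which costs count is unstated, and leaving drugs out would make the control denominator close to zero. The outcome is secondary, and the primary HAMA analysis is unaffected. The definition should be changed before stage 2 data are analysed.

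**What to change.** In section 5.2.3, replace the ratio with an incremental analysis:
1. List the cost items that count and apply the same list to both arms.
2. Report the difference in mean 4-week cost, acupuncture minus control.
3. Report the baseline-adjusted difference in mean HAMA improvement, acupuncture minus control.
4. Report the ratio of the cost difference to the HAMA difference, with a bootstrap 95% interval shown on the cost-effect plane.

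The cost difference reported on its own also speaks directly to the expectation about economic burden in the Discussion.

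The change needs a few sentences, a bootstrap, and the same cost items recorded for controls as for the acupuncture group; the article does not show whether that recording is already planned. No extra patients or visits are needed. The interval for the ratio will be wide if the HAMA difference is near zero, which is why the two differences should be reported separately.
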